**3.3.3 Early termination/closure of the test site**

Trial suspension refers to the fact that the clinical trial has not been completed as planned, and is stopped in the middle of the trial. Reasons for discontinuation of a clinical trial include, but are not limited to:

1) Serious safety issues occurred during the test;

2) In the trial, it was found that there were major errors in the clinical trial protocol, and although the protocol design was good, serious deviations occurred in the implementation;

3) The sponsor requests to suspend (such as financial reasons, management reasons, etc.);

4) Administrative reasons.

In the event of trial abortion, the safety and rights of the participants should be protected as much as possible. The investigator or other staff member cooperates as much as possible to complete the following tasks:

1) Submit all research data that have been generated;

2) Solve all data queries;

3) counting, checking and arranging all unused investigational products;

4) Review the completeness of the study records.

**3.4 Calculation of sample size**

Our calculations of sample size and power are based on the primary outcomes, utilizing a two-sided analysis with a statistical power of 90 % (1 – β = 0.90) and a significance level of α = 0.05. Owing to the lack of prior studies examining cardiovascular ultrasound therapy following PCI, the sample size was determined following an extensive evaluation by a panel of experts. Targeting long-term inflammation and cardiovascular efficacy, they selected high-sensitivity C-reactive protein (hsCRP) as the primary biomarker, given its relevance and the larger sample size required by interleukin 6.

Cardiovascular ultrasound is estimated to reduce hsCRP levels by an average of 4 mg/L. To meet this target, 160 participants (80 per group in a 1:1 allocation) are projected to be needed. Factoring in an anticipated dropout rate of 20 %, the final sample size would be adjusted to 200 participants (100 per group), ensuring adequate statistical power and robustness for the study’s objectives.

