**3.9 Outcomes**

**3.9.1 Primary outcome**

The primary outcome measures will focus on the levels of hsCRP and interleukin-6 in the peripheral serum following 20 cardiovascular ultrasound therapy sessions (i.e., on the 10th day). Comparative analyses will be conducted between the cardiovascular ultrasound therapy intervention and control groups along with pre- and postintervention assessments.

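### Section 3.4 gives 90% power for both primary outcomes, but the sample is sized on hsCRP alone and the text says interleukin-6 needs more patients

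*Protocol*

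**What the plan says.** Protocol section 3.4 opens with a claim that covers more than one outcome: "Our calculations of sample size and power are based on the primary outcomes", two-sided, with 90% power and "a significance level of α = 0.05". The synopsis row on sample size says the same.

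Section 3.9.1 names two outcomes and does not rank them: "The primary outcome measures will focus on the levels of hsCRP and interleukin-6 in the peripheral serum following 20 cardiovascular ultrasound therapy sessions", that is, on day 10. The synopsis row on study outcomes lists the same pair, also unranked.

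Section 3.4 then narrows the basis of the calculation to one marker. It reports that the panel was asked because prior studies were lacking, and that "they selected high-sensitivity C-reactive protein (hsCRP) as the primary biomarker, given its relevance and the larger sample size required by interleukin 6". The only effect given is for that marker: "Cardiovascular ultrasound is estimated to reduce hsCRP levels by an average of 4 mg/L". The sample size follows at once: "To meet this target, 160 participants (80 per group in a 1:1 allocation) are projected to be needed". With 20% dropout this becomes 200 enrolled, 100 per group, and the section concludes that this secures adequate power for the objectives of the study.

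No SD is given for hsCRP. For interleukin-6 there is no effect, SD, sample size or power.

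**The concern.** Three statements do not fit together: 90% power on the basis of the primary outcomes, two unranked primary outcomes, and a sample derived from one of them while the other is said to need more patients. Section 3.4 also speaks of a single primary biomarker where section 3.9.1 has two primary outcome measures.

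What is at stake is the reading of the interleukin-6 result. Under the opening and closing claims of section 3.4, a null day-10 result for interleukin-6 could be reported as the outcome of a test with 90% power. On the protocol's own account that test has less, by an amount the protocol does not disclose.

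**Working it through.** **Inputs from the protocol.** Two-sided α = 0.05, power 0.90, hsCRP difference 4 mg/L, 80 evaluable per arm, dropout 20% (all section 3.4). Section 4.3 expects less than 10% missing data for the primary outcome.

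**Step 1: the plan's own figures.** The dropout step reproduces: 160 / (1 − 0.20) = 200.

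The 80 per arm cannot be reproduced forwards, because no SD is given. Solving backwards with the normal approximation, n = 2(z₀.₉₇₅ + z₀.₉₀)² (SD/Δ)², gives

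SD = 4 × √(80/2) / (1.960 + 1.282) = 4 × 6.325 / 3.242 ≈ 7.80 mg/L.

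The exact t-test gives a standardised effect of 0.516 and SD = 4 / 0.516 ≈ 7.76 mg/L. The 80 per arm is therefore consistent with an hsCRP SD of about 7.8 mg/L. This shows what the figure implies, not what was entered in the software.

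**Step 2: the direction for interleukin-6.** Suppose interleukin-6 needs m per arm for 90% power. Its standardised effect is then d = 3.242 × √(2/m), and its power with n evaluable per arm is approximately

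Φ(d√(n/2) − 1.960) = Φ(3.242 × √(n/m) − 1.960).

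At n = m this is Φ(1.282) = 90%. For any m above n it is below 90%. With n = 80 and m above 80, as section 3.4 says, power for interleukin-6 is below 90%. This step needs no figure from outside the protocol.

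**Step 3: the size, by assumption only.** The protocol gives no m, so the values below are assumed. Worked example for m = 120, n = 80: 3.242 × √(80/120) = 2.647; 2.647 − 1.960 = 0.687; Φ(0.687) ≈ 75%. The table uses the two-sample t-test, which differs from the approximation by at most about 0.3 percentage points.

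| Assumed requirement for interleukin-6, per arm | Power at 80 per arm (planned) | Power at 90 per arm (10% missing) | Power at 100 per arm (none missing) |
| --- | --- | --- | --- |
| 84 | 88.5% | 91.9% | 94.3% |
| 100 | 82.5% | 86.7% | 90.0% |
| 120 | 75.2% | 80.1% | 84.1% |
| 160 | 62.7% | 67.9% | 72.5% |

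The 90-per-arm column is 100 × (1 − 0.10), the lower end of what section 4.3 expects. With 90 per arm, interleukin-6 reaches 90% only if it needs no more than 90 per arm; with 100 per arm, only if it needs no more than 100.

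**The case against.** **The sentence may be garbled.** The usual reason to size a trial on one of two outcomes is that it needs the larger sample. The authors may have meant that hsCRP needs more patients than interleukin-6, and the English is awkward in other places too. On that reading 80 per arm covers both markers. This is a real possibility, but the text attaches the larger sample to interleukin-6 in both section 3.4 and the synopsis. If that is a slip, the rationale is stated backwards and still has to be corrected.

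**The basis is partly disclosed.** A careful reader can see that the sample comes from hsCRP, since only an hsCRP effect is given. That makes a misreading less likely. It does not reconcile the disclosure with the opening claim or with two unranked primary outcomes.

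**The shortfall may be trivial.** This stands. If interleukin-6 needs only slightly more than 80 per arm, its power is close to 90%, and the dropout allowance may cover the gap when missing data stay under 10%. The protocol does not make that argument, and its planning figure is 80 evaluable per arm.

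**Stronger readings.** A reader might infer that the chance of success on both markers is far below 90%. That needs a rule that both must succeed and an assumption about their correlation. The protocol states neither, and two inflammatory markers from the same patients are plausibly positively correlated, so no joint power is given here. A reader might also infer that the hsCRP sample size is wrong. The documents do not show that: without the SD it can be neither confirmed nor refuted.

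**Conclusion.** The point holds as an internal contradiction. Read literally, section 3.4 and the synopsis state 90% power for the primary outcomes, while their own rationale puts interleukin-6 below 90% at the planned 160 evaluable patients. The direction rests only on the protocol's statement that interleukin-6 needs the larger sample.

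The size is unknown. Over assumed requirements of 84 to 160 per arm, power runs from about 88.5% down to 63% at 80 per arm, and from about 92% down to 68% at 90 per arm. It would be too strong to say that the trial is badly underpowered for interleukin-6: the documents give no input from which that follows, and the true gap could be one or two percentage points.

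**What to change.** 1. Confirm which marker needs the larger sample, and on what assumptions the panel concluded this.
2. If it is interleukin-6, limit the 90% claim in section 3.4 and the synopsis to day-10 hsCRP, and state the power that 80 per group gives for interleukin-6 under the panel's own effect and SD. Make section 3.9.1 and the synopsis outcomes agree with the panel's choice of hsCRP, for example with hsCRP as the primary outcome and interleukin-6 as a key secondary outcome.
3. If it is hsCRP, reword the rationale in both places so that it says so. The claim for both outcomes can then stand once the interleukin-6 inputs that support it are given.
4. In either case, state the hsCRP SD actually used in the PASS calculation. The implied value of about 7.8 mg/L serves only as a check and should not be inserted in its place.

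The cost is wording and, if step 2 applies, a less favourable stated power for interleukin-6. Enrolment does not change.

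### The 90% power stated for the primary outcomes rests on hsCRP alone; by the protocol's own words interleukin-6 falls short of it at 80 evaluable per group

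*Protocol*

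**What the plan says.** Section 3.9.1 sets two primary outcome measures, unranked, on day 10: "The primary outcome measures will focus on the levels of hsCRP and interleukin-6 in the peripheral serum following 20 cardiovascular ultrasound therapy sessions". The study outcomes row of the synopsis names the same pair.

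Section 3.4 opens with a statement that covers both: "Our calculations of sample size and power are based on the primary outcomes". It sets 90% power, "utilizing a two-sided analysis" and "a significance level of α = 0.05". It then reports that an expert panel considered the matter and "they selected high-sensitivity C-reactive protein (hsCRP) as the primary biomarker", with the reason "given its relevance and the larger sample size required by interleukin 6".

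The only effect stated is an average hsCRP reduction of 4 mg/L. From it come 160 participants (80 per group), raised to 200 (100 per group) for 20% dropout. The paragraph ends by describing this number as "ensuring adequate statistical power and robustness for the study’s objectives". The sample size row of the synopsis repeats the same text.

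Section 4.3 expects less than 10% missing data for the primary outcome, because participants are inpatients during treatment.

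**The concern.** The opening and closing sentences of section 3.4 claim power for all primary outcomes and for the study's objectives. The middle of the paragraph sizes the trial on one of the two primary outcomes and says that the other needs more patients. These statements cannot all hold at 80 evaluable per group.

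What is at stake is how the interleukin-6 result will be read. A reader who takes the opening sentence at face value would treat a non-significant interleukin-6 comparison as a negative result from a test with 90% power. The protocol's own reasoning does not support that reading.

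**Working it through.** **Inputs.** From section 3.4: power 0.90, two-sided alpha 0.05, hsCRP difference 4 mg/L, 80 evaluable per group, 20% dropout, 100 enrolled per group. From section 4.3: under 10% missing primary-outcome data. Not given: the SD of hsCRP, and any difference, SD or sample size for interleukin-6.

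**The plan's own figures.**
- Dropout step: 160 / (1 − 0.20) = 200. This reproduces.
- The hsCRP sample size cannot be reproduced forwards without an SD. Solved backwards with n per group = 2 × SD² × (1.960 + 1.2816)² / difference², 80 per group implies SD = 4 / (3.2415 × √(2/80)) = 4 / 0.5125 ≈ 7.8 mg/L. At that SD, power for hsCRP at 80 per group is 90%. The missing SD is a separate matter, and the argument here does not depend on it.

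**The logical step.** Let m be the number per group that interleukin-6 needs for 90% power. With n evaluable per group, the normal approximation gives

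power = Φ(3.2415 × √(n/m) − 1.960).

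This equals 0.90 at n = m and is lower whenever n < m. Section 3.4 says that interleukin-6 needs the larger sample, so m > 80, and power at n = 80 is below 90%. This step needs no outside figure.

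**The size, as an assumed range.** The values of m are assumptions; the documents support none in particular. Three values of n are shown: 80 (the basis in section 3.4), 90 (100 × 0.90, the edge of what section 4.3 expects) and 100 (all enrolled participants evaluable). For example, m = 100 and n = 80 gives Φ(3.2415 × 0.8944 − 1.960) = Φ(0.939) = 0.826.

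| Interleukin-6 need per group (assumed) | Power at 80 | Power at 90 | Power at 100 |
|---|---|---|---|
| 90 | 86% | 90% | 93% |
| 100 | 83% | 87% | 90% |
| 120 | 75% | 80% | 84% |
| 160 | 63% | 68% | 73% |

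The exact two-sample t-test gives 0.863, 0.825, 0.752 and 0.627 in the 80-per-group column, against 0.863, 0.826, 0.754 and 0.630 from the approximation. The choice of method does not matter here.

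**The case against.** **The basis is disclosed.** The same paragraph says that hsCRP was selected for sizing, that interleukin-6 needs more, and gives only an hsCRP effect. It never states 90% power for interleukin-6 by name. This is true, and it makes the defect one of scope rather than concealment. The opening and closing sentences still claim more than the calculation delivers, and both outcomes remain primary elsewhere.

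**The sentence may be reversed.** The authors may have meant that hsCRP needs the larger sample and was used for that reason. Interleukin-6 would then have at least 90% power. This cannot be excluded, since the prose is rough in places. But the text gives the larger interleukin-6 requirement as a reason for choosing hsCRP, so the natural reading is the one taken here. On the other reading the sentence itself is wrong and needs correction.

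**Retention may cover the gap.** Section 4.3 expects under 10% missing primary data, so 90 or more per group may be evaluable. Interleukin-6 would then reach 90% if it needs no more than 90 per group, or no more than 100 if nobody is lost. This stands as a possibility. Section 3.4 nevertheless plans on 80 per group and treats the other 20 as a dropout allowance, not as added power.

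**Stronger readings to avoid.** A reader might infer that the trial needs both outcomes positive and multiply the two powers. The documents set no such requirement, and independence of two inflammatory markers in the same patients has no support in them. A reader might also infer that any non-significant interleukin-6 result must be inconclusive. That is too strong, because a narrow confidence interval could still exclude a meaningful effect. Nor does any passage plan to read non-significance as evidence of no effect; that is a risk for readers of the results.

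**Conclusion.** The power statement is wrong as written. On the protocol's own words, the 90% figure applies to hsCRP and not to interleukin-6 at the planned 80 evaluable per group. That conclusion rests on the natural reading of the sentence about interleukin-6 and on no outside number.

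The shortfall cannot be determined. Under the assumed needs of 90 to 160 per group, power at 80 per group runs from about 86% down to 63%. With better retention than section 3.4 assumes, and an interleukin-6 need only slightly above 80, 90% could still be reached. A reader might conclude that interleukin-6 is badly underpowered or that more patients must be enrolled; the documents give no figure that supports either.

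**What to change.** No additional enrolment is needed. In section 3.4 and the sample size row of the synopsis:

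- Limit the statement of 90% power to hsCRP.
- Give the interleukin-6 difference and SD that the expert panel used, and the resulting power at 80 evaluable per group.
- Remove the closing claim of adequate power for the study's objectives, or limit it to hsCRP.
- If the sentence about interleukin-6 was meant the other way round, correct it and say that hsCRP has the larger requirement.

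Reconcile section 3.9.1 and the study outcomes row of the synopsis, which list two unranked primary outcomes, with section 3.4, which singles out hsCRP as the primary biomarker. Report interleukin-6 with its confidence interval, and do not take non-significance alone as evidence of no effect.

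The cost is a revision of the sample size paragraph in its two places and a short clarification of the outcome lists. On the natural reading, the stated power for one primary outcome becomes less favourable. Trial conduct does not change.

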**3.5 Randomization and blinding**

Using a randomized 1:1 ratio, participants will be allocated into either of two groups: the cardiovascular ultrasound therapy group and the control group. This process will be facilitated by a computer-generated randomization sequence. To uphold the integrity of the allocation process, a team of research assistants not involved in clinical care or outcome assessment will meticulously craft sequentially numbered, opaque, sealed envelopes based on the predefined randomization list. This meticulous approach will ensure the safeguarding of confidentiality and the autonomy of allocation data. When appropriate, the assistants will open envelopes and ensure the coordination of therapeutic interventions.

Given the distinctive visual and operational characteristics of cardiovascular ultrasound therapy, the assignment results will not be concealed from the attending physicians or the patients. Only the investigative team members responsible for the collection of primary outcome data will remain masked. Consequently, the study design adheres to the framework of a nonblinded controlled trial. Patients will retain the prerogative to decline study participation, in which case they would receive standard care only.

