**3 Study program**

**3.1 Study design and ethical approval**

This nonblinded, multicenter, parallel-group, randomized (1:1) controlled study will be conducted in 10 large hospitals in China, including Qilu Hospital of Shandong University, Qingdao Municipal Hospital, Yantai Yuhuanding Hospital, Linyi People’s Hospital, Tengzhou Central People’s Hospital, Weifang People’s Hospital, Jining No.1 People’s Hospital, Weihai Central Hospital, Liaocheng People’s Hospital, Dongying People’s Hospital, and Qilu Hospital of Shandong University (Qingdao). These hospitals were selected because of their significant experience and ability to recruit for PCI in cardiology as well as their ability to collaborate across disciplines to ensure that patients receive comprehensive treatment and rehabilitative support. The study protocol was reviewed and approved by the Ethics Committee of Qilu Hospital of Shandong University and other participating institutions (Ethics Committee reference number KYLL-202308-006). The study was registered on ClinicalTrials.gov, ID: NCT06640400.

Participants in this study will be recruited from the aforementioned medical institutions. Inclusion criteria call for hospitalized patients diagnosed (through laboratory and imaging tests) with CAD requiring PCI ^[16]^. Following consent from the patients or their family members, screening procedures will be conducted by medical professionals to ensure compliance with the eligibility criteria. Only those individuals meeting all recruitment criteria and no exclusion criteria will be included in the study.

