**3.7.2 Intervention description**

Participants allocated to the intervention group will undergo a 10-day regimen utilizing a medical cardiovascular ultrasound therapy device (838C-M-L-I/II, Shenzhen, China). The ultrasound instrument is equipped with a sound head comprising five transducer units operating at an ultrasonic frequency of 0.84 MHz with a sound intensity range of 1 W/cm^2^–1.25 W/cm^2^. The therapeutic ultrasound sessions require a controlled environmental temperature. Patients will assume the supine position, exposing the precordial region, with the 5-pronged head positioned parallel to the heart’s long axis; it should cover the entire precordial region including the right and left coronary arterial trunks and the aortic root (Fig.1). The five transducer units function sequentially in a scanning pattern, with each unit operating for 5 seconds and transitioning with a 0.5-second interval, following a clockwise rotation until the treatment has been completed. The cardiovascular ultrasound therapy device operates in a pulsed mode, and each treatment session lasts for 20 minutes; there would be two daily sessions for a total of 20 treatments. The control group was not given extracorporeal cardiac ultrasound therapy. Participants in the control group will not receive cardiovascular ultrasound therapy. cardiovascular ultrasound therapy will be assessed at baseline (24th-hour post-PCI), on the 10th day, and at the end of the first and third months post-intervention. If it is necessary to change the medication regimen as much as possible, if it is necessary to change the medication regimen, it should be decided after evaluation by the investigator, and if the medication regimen that does need to be changed has an impact on the test results, the patient should be excluded and the reasons for changing the medication regimen should be recorded in detail.

[figure not shown]

Fig. 1. Diagram of ultrasound head placement.

A: Patients undergoing cardiovascular ultrasound therapy. B is used in patients with occlusion of one coronary artery and C is used in patients with occlusion of both coronary arteries.

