**(5) Echocardiography**

The echocardiogram parameters will encompass E/e' ratio, left ventricular ejection fraction (LVEF), and wall thickening fraction (WTF). WTF is defined as [(end-diastolic wall thickness − end-systolic wall thickness)/ end-diastolic wall thickness] × 100 (%).

Echocardiographic assessments will be conducted by certified sonographers proficient in thoracic echocardiography. This will be done at multiple time points: at baseline (24th hour post PCI), on the 5th and 10th days, and at the end of the 1st and 3rd months post intervention.

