**(6) Ultrasound examination of carotid plaques**

Ultrasonography of carotid plaques includes their location, size (length × width), and morphology as well as the intima-media thickness (IMT) and Crouse’s score of the common carotid artery.

A certified sonographer proficient in examining the carotid arteries will perform ultrasound evaluations at multiple time points: at baseline (24th hour post PCI); on the 5th and 10th days; and at the end of the 1st and 3rd months post intervention.

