**(7) Six-minute walk test**

The six-minute walk test (6MWT) quantifies the maximal distance an individual can walk in 6 minutes, serving as an indicator of the patient's exercise capacity and cardiorespiratory fitness during routine physical activities.

A certified cardiologist will conduct the 6MWT at various time points, including at enrollment, on the10th day, and at the end of the 1st and 3rd months post intervention.

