**(9) Tools for mental health assessment**

The Patient Health Questionnaire-9 (PHQ-9) is a critical instrument for the screening, diagnosis, and assessment of depression, enabling the measurement of its severity. Concurrently, the 7-item Generalized Anxiety Disorder Scale (GAD-7) enables the evaluation of generalized anxiety disorder. Similarly, the Pittsburgh Sleep Quality Index (PSQI) stands as a widely recognized assessment tool for determining sleep quality, and the Seattle Angina Questionnaire (SAQ) functions as a self-administered assessment tool designed to evaluate specific functional status and quality of life among individuals with CAD.

Mental health assessments will be conducted by certified psychologists at various time points: at baseline (24th hour post PCI), on the 10th day, and at the end of the 1st and 3rd months post intervention.

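### Masking covers only the staff who collect the serum primary outcome; none is provided for those who assess echocardiography, carotid ultrasound and the 6-minute walk

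*Protocol*

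**What the plan says.** Section 3.1 describes the trial as "This nonblinded, multicenter, parallel-group, randomized (1:1) controlled study". Section 3.5 says that, because of how the therapy looks and is operated, "the assignment results will not be concealed from the attending physicians or the patients", and then sets the limit of masking: "Only the investigative team members responsible for the collection of primary outcome data will remain masked".

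Section 3.9.1 defines the primary outcome as serum hsCRP and interleukin-6 on day 10. Section 3.7.2 gives the control condition: "Participants in the control group will not receive cardiovascular ultrasound therapy". No sham procedure is described.

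Section 3.9.2 names an assessor for each of the operator-dependent secondary outcomes:

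- Echocardiography: "Echocardiographic assessments will be conducted by certified sonographers proficient in thoracic echocardiography"
- Carotid ultrasound: "A certified sonographer proficient in examining the carotid arteries will perform ultrasound evaluations"
- 6-minute walk test (6MWT): "A certified cardiologist will conduct the 6MWT at various time points"
- Questionnaires: "Mental health assessments will be conducted by certified psychologists"

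None of these items mentions masked assessment, central or masked reading, or keeping the assessor apart from the treating team.

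**The concern.** Masking an assessor does most good where the assessor's judgement enters the result. Here it is given to two serum assays, where observer judgement matters least. It is not given to caliper measurements and image readings, or to the person who instructs and encourages a patient during a walk test. A sonographer who knows the arm can, without intending to, choose a frame, a plaque boundary or a wall-thickness measurement that favours expectation. A supervisor who knows the arm can encourage patients unevenly.

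Section 2 names cardiac function and carotid plaque among the aims, and exercise capacity is assessed as a secondary outcome. A difference between arms on any of these could not be cleanly separated from observer expectation, and part of that ambiguity is avoidable.

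**Working it through.** The point turns on the text, so the masking rule is set beside each outcome.

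| Outcome | Assessor named (Protocol 3.9) | Depends on operator? | Masking provided (Protocol 3.5)? |
| --- | --- | --- | --- |
| hsCRP, interleukin-6 | Staff collecting primary outcome data | Little (assay) | Yes |
| E/e', LVEF, wall thickening fraction | Certified sonographers | Yes | No |
| Carotid plaque, intima-media thickness | Certified sonographer | Yes | No |
| 6MWT distance | Certified cardiologist | Partly (supervision); also patient effort | No |
| PHQ-9, GAD-7, PSQI, SAQ | Certified psychologists; SAQ described as self-administered | Mainly patient report | No |

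**Does other text extend the masking?** No. Section 3.5 does mention people uninvolved in clinical care or outcome assessment, but these are the research assistants who prepare the randomization envelopes.

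**Does the stated reason cover these assessors?** The therapy's appearance and operation explain why patients and attending physicians know the arm. They do not explain why a sonographer measuring a stored image needs to know it. Echocardiography and carotid ultrasound are also done at the end of months 1 and 3, after the 10-day course is over.

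**How much could it matter?** The protocol gives no figure to reproduce and no size of bias, so this part is illustration only.

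- Inputs: 80 per arm (section 3.4, before the dropout allowance); two-sided 5% level (sections 3.4 and 4); no true effect; an assumed systematic assessment difference of b standard deviations between arms.
- Shift of the test statistic: d = b / √(2/80) = b × 6.325.
- Chance of a significant result (normal approximation): 1 − Φ(1.96 − d) + Φ(−1.96 − d).

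| Assumed b | d | Chance of p < 0.05 |
| --- | --- | --- |
| 0 | 0 | 5.0% |
| 0.1 | 0.632 | 9.7% |
| 0.2 | 1.265 | 24.4% |

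A two-sample t-test calculation gives 9.6% and 24.2% for the last two rows, which is the same for practical purposes. With all 100 per arm analysed, the normal approximation gives 10.9% and 29.3%. A larger sample does not dilute a systematic bias; it makes a false finding more likely.

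**The case against.** The strongest reply is that this is a declared design choice, not an error. The protocol calls itself nonblinded, gives a reason, and places masking on the outcome that drives the sample size. The affected outcomes are all secondary, and the inflammatory, lipid, endothelial and myocardial-injury markers are blood measurements. This stands, and it limits the weight of the point. It does not remove it, because the reason given does not reach the people who measure images.

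A reader might go further than the text in four ways:

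- **That the assessors are told the allocation.** The protocol does not say so. It leaves them outside the masked group and names only attending physicians and patients as knowing the arm. The supportable statement is that masking is not provided for and that they may know.
- **That separate staff already do these tests, so the change is free.** The protocol names professions, not separation from the treating team. The walk test is run by a cardiologist, who could be the patient's attending physician.
- **That masking assessors would protect the questionnaires.** The patient knows the arm and the SAQ is self-administered, so most of that bias would remain. The same is partly true of effort in the 6MWT.
- **That the primary result is compromised.** Nothing here supports that: the measurement is an assay and its collectors are masked.

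It is also fair to object that the assumed 0.1 and 0.2 SD have no source in the documents. They show what a bias of that size would do, not that one exists.

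**Conclusion.** The point holds for echocardiography, carotid ultrasound and supervision of the 6MWT. Section 3.5 confines masking to primary-outcome collection, and nothing in section 3.9.2 adds to it. It is strongest for the two imaging outcomes and weaker for the walk test, where the patient's own knowledge also acts.

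This is a worthwhile, low-cost improvement to secondary outcomes in an openly declared nonblinded trial; it is not a flaw in the primary comparison. The size of any bias is unknown. The rates of about 10% and 24% per outcome are conditional on the assumed 0.1 and 0.2 SD with 80 per arm, and the case does not depend on them.

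**What to change.** In section 3.5, replace the sentence that limits masking with text to this effect:

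> In addition to the staff collecting primary outcome data, the sonographers who perform and read echocardiography and carotid ultrasound will not be told the treatment arm, will not deliver the therapy, and will read and measure images identified by study number only. Where site staffing allows, the 6-minute walk test will be supervised by a cardiologist who is not the patient's attending physician and is not told the arm. PHQ-9, GAD-7, PSQI, SAQ and effort in the walk test remain open to bias because patients know their arm; these results will be interpreted as open-label and supportive.

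The cost is a wording change, a site instruction and some scheduling effort. A site whose cardiologists all treat trial patients may be unable to meet the walk-test condition, which is why it is made conditional. Some accidental unmasking should be expected, chiefly at the in-hospital assessments on days 5 and 10.
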